### Personnel

Two study coordinators (one in NSW and one in SA) will be responsible for project management. Allied health professionals (Implementation clinician, Implementation physiotherapist/Exercise Physiologist, Implementation Pharmacist, Implementation Dietitian) will provide extra sessions of physiotherapy, pharmacy, and dietetics for each ward while the person is an inpatient. A therapist will act as a Community Implementation Facilitator will work with people upon discharge from hospital to assist with implementation of the frailty management strategies and primary network liaison. 

### Intervention

Patients admitted to the wards taking part in this study are screened for eligibility. Baseline frailty is measured using the FRAIL scale [8] and a score of 3 and above indicates frailty. If the person has been admitted to a ward during the control phase of the research study, they will receive usual care as provided by the ward staff and their general practitioner and other health service providers. Participants admitted to the ward during the intervention phase will receive an individualised intervention designed to treat the identified components of frailty, along with the community implementation visit(s), telephone calls, and support from their general practitioner (GP) once discharged. Additional file 1 outlines the TIDier framework [26] describing the FORTRESS intervention. Intervention is divided into two phases:

#### The Hospital Intervention

Intervention participants will receive referrals for physiotherapy, dietitian and pharmacy review. A tailored Frailty Management Plan will be developed by the multidisciplinary team and documented in the electronic medical record. A tailored exercise program involving resistive training prescribed by the physiotherapist and/or exercise physiologist. Malnutrition screening, nutrition education and advice will be provided by the dietitian. When indicated, the pharmacist will undertake medication history and review at hospital admission and medication reconciliation at discharge, provide education on medication changes and prepare a medication management plan. Indicators for pharmacy review include those experiencing frailty side effects of medication and polypharmacy. The pharmacist will document in the Frailty Management Plan any changes in medication regimen in hospital and the reasons for change; and recommend referral for a Home Medicines Review to be completed within 3 months of discharge. Other frailty interventions such as commencing Vitamin D supplementation may occur when indicated by the medical team or pharmacist. Prior to discharge from hospital, the Frailty Management Plan will be discussed with the participant and/or their significant other who will also receive a copy. Any nutrition and/or exercise recommendations will be detailed and provided in a handout for participants. A copy of the Frailty Management Plan will be sent via fax or secured electronic messaging to the participant’s GP along with all other relevant discharge information.

#### The Community Intervention

A health professional employed as a Community Implementation Facilitator will review the participant’s motivation and adherence to the Frailty Management Plan recommendations after discharge from hospital and will liaise with the person’s general practice to facilitate ongoing frailty management. The participant will receive a home visit from the Community Implementation Facilitator within a week of discharge, and 2–4 telephone calls in the subsequent 4–6 weeks post discharge. The role of the visits and telephone calls are to support adherence to frailty management plan recommendations, including:Clarify the purposes of the study and answer any questions that the participant or their carer/significant other may have, that have arisen since the participant’s dischargeEnsure study participants understand and can perform the prescribed exercises in their home environmentEncourage study participants to continue with the nutrition interventions at homeAssist/encourage participants to make an appointment to see their GP as soon as practicable following dischargeContact the GP or Practice Nurse with suggested ongoing management of the participant’s Frailty Management Plan

The pharmacist will telephone participants post-discharge to provide detailed education on current medications and recent hospital medication changes. The pharmacy telephone call will entail education to the participant about their medications and encourage them to adhere to the medication management plan prepared in hospital. The Home Medicines Review will be recommended to be initiated by the GP to ensure any medication changes will be implemented by the GP. The Home Medicines Review report will be sent to the participant’s GP, and the study coordinator where available.

### Outcome measurements

#### Primary outcome

The primary analysis will compare length in days of non-elective hospital admissions after the index admission during 12 months of follow up between intervention and control conditions. Electronic medical records for each participant will be reviewed at 3 months and 12 months for non-elective public readmissions at hospitals within the included local health district. Private hospital readmissions are not available on the public electronic medical records, therefore will be determined by participant self-report to a blinded outcome assessor at 3 months and 12 months. Reason for readmission will also be gained from electronic medical record and participant self-report, to determine Diagnostic Related Groups (DRGs).

#### Secondary outcomes

Frailty status at baseline, 3 months and 12 months measured using the FRAIL Scale [8].Quality of life at baseline, 3 months and 12 months measured using the EQ-5D-5L [27].Time-to-event of readmission, and readmission rates at 3 months and 12 months.

Baseline measures are assessed by the study Implementation Clinician on the ward at admission. Follow-up outcome assessment will take place via telephone at 3 and 12 months by a health professional masked to group allocation. Each assessment will include administration of the FRAIL Scale to measure frailty and EQ-5D-5L to measure quality of life. Data regarding overnight non-elective hospital readmissions will be obtained from participant self-report, and from public hospital electronic medical records for hospital readmissions.

#### Additional measures

Participants will be asked to self-report their weight and current medications at 3- and 12-month outcome assessments. Current medications will be cross-checked through participant’s pharmacists and Home Medicine Review report where available. Covariables to be considered will include age, sex, degree of frailty at index admission, number of hospitalisations in the preceding 12 months, cognition (MMSE score), and primary admission diagnosis for the index admission and for readmissions.

The hybrid nature of this trial allows understanding of both effectiveness and implementation. Figure 2 describes the conceptual model of evaluation [28]. A process evaluation will be conducted concurrently to describe the adaptation, scale and spread of FORTRESS intervention and details will be described in a separate paper. Details are available through the trial registry.

**Fig. 2 Fig2:**
[figure not shown]
Conceptual model of hybrid II implementation research for FORTRESS trial

### Sample size

The projected enrolment is approximately 732 participants from the six wards over 16 months. This sample size enables detection of a mean difference of 35 days versus 50 days in total length of hospital stay at readmission after the index admission during 12 months of follow up, with 80% power at significance level 5%, allowing for 10% mortality, 10% dropout, and a design effect of 1.75 for clustering by wards.

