## Methods

### Design

The FORTRESS trial is a multi-site hybrid type II stepped wedge, cluster randomised trial to be conducted over three years (see Fig. 1). This study protocol is reported in accordance to the Standard Protocol Items: Recommendations for Intervention Trials (SPIRIT) checklist available as supplementary file. The hybrid type II trial approach [20] allows testing of the implementation strategy (Implementation Facilitation [21]) and testing the outcomes of the intervention (screening for frailty and use of appropriate interventions).

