## Discussion

Frailty is associated with poorer outcomes for individuals and prevalence is likely to increase due to an ageing population. There is evidence that intervention can effectively reverse frailty and Asia Pacific Guidelines recommend screening and multidisciplinary intervention [16, 22, 23]. This study investigates the efficacy of implementing frailty guidelines for hospitalised older adults and explores the process of implementation in this setting. The results will provide important information which can be used by health care policy makers, managers and clinicians worldwide.

Frail older people with chronic and complex health conditions have high re-admission rates with approximately 25% of older people being readmitted within three months of hospital discharge [31]. Continuity and integration of care following discharge from the acute setting is consistently recommended but difficult to achieve given the current divide between funding for acute and primary care settings. The FORTRESS study aims to work across settings to address frailty identified in a hospital environment. Evidence for cost-effectiveness of preventive, integrated care is generally limited due to a wide variety in study populations, interventions and evaluations [32]. However, previous studies have demonstrated that a multicomponent interdisciplinary frailty intervention is both more effective and less costly than usual care [24]. The FORTRESS study aims to demonstrate that the cost of delivering the intervention will be significantly outweighed by the cost of hospital re-admissions.

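### The stated 80% power rests on a design effect of 1.75 described as covering ward clustering only; adjusting a six-ward stepped wedge for calendar time would usually need a larger one

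*Protocol article*

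**What the plan says.** The Design section states: "The FORTRESS trial is a multi-site hybrid type II stepped wedge, cluster randomised trial to be conducted over three years". The Randomisation procedure section adds that the time at which each ward moves to the intervention is randomised, stratified by site.

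The Sample size section gives the enrolment: "The projected enrolment is approximately 732 participants from the six wards over 16 months". It says this allows "detection of a mean difference of 35 days versus 50 days in total length of hospital stay at readmission", "with 80% power at significance level 5"%, "allowing for 10% mortality, 10% dropout, and a design effect of 1.75 for clustering by wards". No standard deviation, ICC, number of steps or derivation of 1.75 appears in the text. Fig. 1, which shows the schedule, is not reproduced in the copy reviewed.

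**The concern.** In a stepped wedge, the share of wards under the intervention rises with calendar time. A valid treatment estimate therefore has to be adjusted for period, and the adjustment costs information. This cost is separate from within-ward correlation and is present even when the ICC is zero. The only design allowance in the power statement is attributed to ward clustering.

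If 1.75 covers clustering alone, the stated power is too high for most ordinary schedules. A reader of a null result could then place more weight than is justified on the trial's ability to detect a 15-day reduction.

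**Working it through.** **Inputs.** From the Sample size section: N = 732, six wards, difference 50 − 35 = 15 days, power 80%, significance level 5%, losses 10% + 10%, design effect 1.75. Assumed: a two-sided test, additive losses (0.80 retained), equal ward sizes, and six or three steps.

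**1. The plan's own figure.**
- 732 × 0.80 = 585.6 analysed; 585.6 / 1.75 = 334.6 effective; 167.3 per arm.
- With 1.960 + 0.842 = 2.802, 80% power for 15 days needs SD = 15 / (2.802 × √(2/167.3)) = 49.0 days.

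So 732 is what a two-arm comparison of means with SD about 49, inflated by 1.75, would give. The SD is back-solved, so this shows consistency and does not verify the figure.

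**2. The ICC implied by 1.75.** Reading 1.75 as 1 + (m − 1) × ICC:
- m = 732/6 = 122 enrolled per ward: ICC = 0.75/121 = 0.0062.
- m = 97.6 analysed per ward: ICC = 0.75/96.6 = 0.0078.

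**3. Cost of time adjustment at ICC = 0.** With fixed period effects, the information on treatment is Σ n_j p_j(1 − p_j), where n_j is the number of participants in period j and p_j the share of wards treated. An individually randomised 1:1 trial has N/4. The design effect is the ratio of the two.
- Six steps, seven equal periods: Σ p(1 − p) = (0+5+8+9+8+5+0)/36 = 35/36. Information = (N/7)(35/36) = 5N/36. Design effect = (1/4)/(5/36) = 1.80.
- Three steps, four equal periods: Σ p(1 − p) = 4/9. Information = N/9. Design effect = 9/4 = 2.25.
- End periods of half length: (1/4)/((1/6)(35/36)) = 1.54 with six steps and (1/4)/((1/3)(4/9)) = 1.69 with three.

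**4. Design effect at ICC > 0.** I used the Hussey–Hughes generalised least squares variance with fixed period effects and an exchangeable ward effect. The ward covariance is V = diag((1 − ICC)/m_j) + ICC × J, where m_j is the number in one ward-period and J is a matrix of ones. The variance of the treatment effect was divided by 4/N.

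**5. Power.** Power = Φ(2.802 × √(1.75/DE) − 1.960). The SD cancels, because 732, 1.75, 80% and 15 days together fix it. For example, DE = 2.14 gives 2.802 × 0.904 − 1.960 = 0.574, which is 72%.

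Results for 97.6 analysed per ward:

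| ICC | End periods | Steps | Design effect | Power |
|---|---|---|---|---|
| 0 | full | six | 1.80 | 79% |
| 0 | full | three | 2.25 | 70% |
| 0.0062–0.0078 | full | six | 2.14–2.19 | 71–72% |
| 0.0062–0.0078 | full | three | 2.61–2.67 | 62–63% |
| 0.0062–0.0078 | half or quarter | six or three | 1.77–2.14 | 72–79.5% |
| 0.0062–0.0078 | one-tenth or less | six or three | 1.56–1.77 | about 80–84% |
| 0.02 | full | six | 2.47 | 66% |
| 0.02 | full | three | 2.94 | 58% |
| 0.02 | most favourable tried (near-absent ends, six steps) | six | 2.10 | 72.5% |

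**6. Detectable difference at 80% power.** 15 × √(DE/1.75) gives 16.6–16.8 days (DE 2.14–2.19) and 18.3–18.5 days (DE 2.61–2.67), against the planned 15.

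No small-sample correction for six wards and no site-specific period effects are included.

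**The case against.** The strongest reply is that no arithmetic error has been shown. The SD is back-solved, the schedule is in a figure that was not available, and the article does not say how 1.75 was obtained. A condensed article may leave the ICC, SD and derivation to a fuller document, so their absence is not a fault. This stands, and it limits the conclusion.

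The layout matters too. At ICC 0 the time-adjusted design effect exceeds 1.75 with full-length end periods, but not once they are half length (1.54 or 1.69). At the implied ICC, end periods of one-tenth of a period or less bring power back to about 80%. A reader might infer that the trial does not have its stated power. The documents do not support that, because such a schedule with so small an ICC cannot be excluded.

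It may also be said that a smaller SD would rescue the figure: at SD 45 and design effect 1.75, power would be 86%. But 732 would then not be the number needed for 80% under the stated allowances, so this is a different calculation.

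Nor does leaving period out of the model help. The Statistical analysis section names ward clustering and confounders, and the detailed model may be specified elsewhere. Without a period term the design effect falls to about 1.0–1.2, but treatment is then confounded with calendar time.

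Finally, a reader might take the Discussion's figure of "approximately 25% of older people being readmitted within three months of hospital discharge" as evidence that the assumed variance is too small. It is a background figure for older people in general and is not given as a planning input. Turning it into a 12-month variance for this frail population needs several assumptions that the article does not make, so no weight is placed on it.

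**Conclusion.** The concern holds in conditional form. The stated power relies on an allowance that, by its own wording, covers ward clustering and not adjustment for time. Under equal periods and the ICC implied by 1.75, power is about 71–72% (six steps) or 62–63% (three steps). With half- or quarter-length end periods it is about 72–79.5%. Only near-absent end periods combined with an ICC below about 0.01 restore 80%.

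An ICC that low is not assured. The Randomisation procedure section balances wards on typical length of stay and, where possible, readmission rates, which suggests that wards are expected to differ on matters close to the primary outcome. At ICC 0.02, every six- or three-step layout tried gave at most about 72.5%.

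These results rest on an assumed schedule, an assumed ICC, the reading of 1.75 as a clustering-only factor, and the plan's two-sided normal approximation. They show that the 80% is not supported for conventional layouts. They do not show that it is false for the schedule actually used.

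**What to change.** Recompute power, or the difference detectable with 80% power, for the same 732 participants. Use a stepped-wedge formula or a simulation with the actual schedule and ward-period sizes, fixed period effects, and a range of ICCs (for example 0.005 to 0.05, since none is given in the article). State whether 1.75 was meant to include time adjustment. Replace the 80% statement with the result unless the calculation confirms it.

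The cost is a few hours of calculation and possibly a less favourable published figure. No extra patients and no change to trial conduct are needed.

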**Fig. 1 Fig1:**
[figure not shown]
Overview of the FORTRESS stepped wedge design Participants and sites. SALHN – Southern Adelaide Local Health Network, South Australia. HKH – Hornsby Ku-ring-gai Hospital, New South Wales

The FORTRESS trial builds on previous research conducted by members of the research team. Cameron et al., [22] evaluated the efficacy of a multicomponent interdisciplinary intervention with community dwelling older people after completion of their contact with health services in the Frailty Intervention Trial (FIT). Interventions included multiple sessions of physiotherapy and dietetics, with limited comprehensive geriatric assessment over a period of 12 months. Results of FIT included reduced frailty, improved physical performance, and increased degree of independence for community dwelling older people [22, 23]. Economic evaluation revealed that in very frail older people residing in the community, the multicomponent interdisciplinary intervention was both more effective and less costly than usual care [23, 24].

The protocol for this study has been approved by the Northern Sydney Local Health District Human Research Ethics Committees and is registered at www.ANZCTR.org.au (ACTRN12620000760976p).

The FORTRESS trial will be conducted across six inpatient wards at two different states (Hornsby Ku-ring-gai Hospital, Northern Sydney Local Health District in New South Wales, and Southern Adelaide Local Health Network in South Australia). Older people will be included if they are aged 75 years or older; admitted to the six wards included within the participating local health districts; assessed as frail (score of 3 or above out of 5 on the FRAIL scale [8]); living at home in the community; and score 24 or above out of 30 on the Mini Mental State Exam [25]. People will be excluded if they are admitted to hospital with a new diagnosis of stroke (people with acute stroke are admitted to specialised units in both participating hospitals), have an illness likely to be associated with a life expectancy of < 12 months (assessed on the modified version Illness Severity Rating [20]); are unable to cooperate with the intervention program; were not mobile prior to admission; or reside in a residential aged care home. 

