### Randomisation procedure

Transition to the intervention phase will be randomised by ward with stratification by site and using minimisation with a random component to optimise baseline and sequential balance. To do this the minimisation algorithm will use anticipated ward characteristics including the type of ward, typical length of stay, high or low tendency to discharge to a day rehabilitation ward rather than home and, where possible, typical readmission rates at that ward.

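### The only design effect in the sample size, 1.75, is attributed to ward clustering with no stated allowance for calendar period, so the 80% power is not supported as derived and is probably optimistic

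*Protocol article*

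**What the plan says.** The Design section describes a "multi-site hybrid type II stepped wedge, cluster randomised trial". The text after Fig. 1 gives six inpatient wards in two states, and the Randomisation procedure section adds: "Transition to the intervention phase will be randomised by ward with stratification by site".

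The Sample size section states: "The projected enrolment is approximately 732 participants from the six wards over 16 months". The target is "detection of a mean difference of 35 days versus 50 days in total length of hospital stay at readmission", "with 80% power at significance level 5" per cent, "allowing for 10% mortality, 10% dropout, and a design effect of 1.75 for clustering by wards".

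The section gives no ICC, standard deviation (SD) or dispersion, number of steps or period lengths. The step layout is in Fig. 1, which is not available here. The Statistical analysis section accounts for ward clustering and patient-level confounders. It does not name a period term, which may be left to the analysis plan and is not itself the point here.

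**The concern.** In a stepped wedge every ward starts under control and ends under intervention, so treatment is confounded with time. A valid estimate removes the period effect, and this loses information even when patients within a ward are uncorrelated. An allowance for ward clustering alone does not pay for that loss.

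The stated power governs how a null result will be read. If the chance of missing a true 15-day reduction is materially above 20%, a null result would be over-interpreted as evidence against it.

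**Working it through.** **Inputs.** From the Sample size section: N = 732 over six wards (122 per ward), 35 versus 50 days, 80% power, 5% significance (taken as two-sided), design effect (DE) 1.75, 10% mortality and 10% dropout. Assumed: six steps of one ward or three steps of two, an all-control first period and an all-intervention last period, different patients in each period, and the ICC (ρ).

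**The plan's own figure.** With no SD given, 732 can only be back-solved. With an SD of 49 days: 2 × (1.96 + 0.842)² × 49² / 15² = 167.5 per group, or 335 in total; × 1.75 = 586.3; / 0.80 = 732.9. An SD of 50 with attrition applied as × 1.20 gives 735. So 732 is consistent with a two-group calculation times 1.75, but one free parameter was chosen to make it fit, and this does not show how 732 was obtained.

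**Period-adjusted design effect.** The model has fixed period effects, a treatment effect and a random ward effect (Hussey–Hughes). The variance of the treatment effect by generalised least squares is divided by 4σ²/N, the variance for an individually randomised comparison of the same size. For k steps, equal periods and n patients per ward-period this has a closed form:

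DE = {[1 + ρ(kn + n − 1)] / [1 + ρ(kn/2 + n − 1)]} × (1 − ρ) × 3k / [2(k − 1)]

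At ρ = 0 only the last factor remains:
- k = 6: 18/10 = 1.80
- k = 3: 9/4 = 2.25

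Both exceed 1.75 before any ward correlation is added.

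**Illustrative ICC.** If 1.75 = 1 + (122 − 1)ρ, then ρ = 0.75/121 = 0.0062. The document does not state this formula.
- k = 6, n = 122/7 = 17.43: (1.750/1.426) × 0.9938 × 1.80 = 2.20
- k = 3, n = 122/4 = 30.5: (1.750/1.467) × 0.9938 × 2.25 = 2.67

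Using the roughly 99 patients per ward left after attrition (ρ = 0.0077) gives the same values to within 0.01.

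**Power at 732.** Anchored on the plan's 80% at DE 1.75, so that the unknown SD and the attrition cancel: power = Φ(2.802 × √(1.75/DE) − 1.96).

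| Layout | ρ = 0 | ρ = 0.0062 | ρ = 0.02 | ρ = 0.05 |
|---|---|---|---|---|
| Six steps, equal periods | 1.80 (78.9%) | 2.20 (70.6%) | 2.54 (64.2%) | 2.72 (61.3%) |
| Three steps, equal periods | 2.25 (69.5%) | 2.67 (62.1%) | 3.01 (57.0%) | 3.16 (54.9%) |
| Six steps, half-length first and last periods | 1.54 (84.7%) | 1.96 (75.5%) | 2.35 (67.6%) | 2.58 (63.5%) |
| Three steps, half-length first and last periods | 1.69 (81.4%) | 2.14 (71.7%) | 2.57 (63.7%) | 2.83 (59.7%) |
| Six steps, first and last periods 1/20 of a step | 1.31 (89.9%) | 1.75 (80.1%) | 2.21 (70.2%) | 2.54 (64.3%) |
| Three steps, first and last periods 1/20 of a step | 1.18 (92.6%) | 1.70 (81.2%) | 2.36 (67.4%) | 2.94 (58.0%) |

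The detectable difference at 80% power is 15 × √(DE/1.75): 16.8 days at DE 2.20 and 18.5 days at DE 2.67.

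**Where 1.75 would suffice.** Solving DE = 1.75 with the same model gives these upper limits for ρ:
- Half-length end periods: about 0.0026 with six steps, about 0.0006 with three.
- End periods one-tenth of a step: about 0.006 in both layouts (three steps at ρ = 0.0062 gives 1.744).

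**Without period terms.** At ρ = 0.0062 and equal periods the DE is 1.07 to 1.11 and power 94% to 95%, but any time trend then stays in the treatment effect.

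**The case against.** The strongest reply is that the inputs needed to contradict 80% are not in the text. The number of steps and the period lengths are in Fig. 1, no ICC is given, and the origin of 1.75 is not described. A short phrase in a condensed article does not prove that period was ignored. Some period-adjusted layouts do give a DE of 1.75 or less: 1.63 with six steps and half-length end periods at an ICC of 0.001, and 1.65 (six steps) or 1.67 (three) with quarter-length end periods at 0.003. So 1.75 could be a genuine stepped-wedge design effect.

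Most of this stands, and it rules out three stronger readings:
- A reader might infer that the trial's power is 62% to 71%. That pair belongs to one assumed ICC and two assumed layouts.
- A reader might infer that 732 was calculated as a parallel design. The SD of 49 was back-solved, so the match is not evidence.
- A reader might infer that only leaving period out brings the DE below 1.75. Short end periods with a very small ICC do so too.

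The reply does not rescue the stated derivation. The article says what its design effect covers, and that is ward clustering. The value matches neither the analysis without period nor the adjusted analysis with equal periods, and the conditions under which it would be right are narrow and unstated. The absence of a named period term does not help either: with such low ICCs and no period term, an inflation of 1.75 would not be needed.

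**Conclusion.** The point holds in conditional form. The Sample size section attributes its one design effect to ward clustering and states no allowance for period adjustment. With six wards and equal periods, 1.75 is too small at every ICC examined from 0 to 0.1, so the 80% is unsupported as derived and probably optimistic.

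The size depends on the layout. At an ICC of about 0.006, power is about 71% with six equal steps and 62% with three. Across three or six steps, equal or shortened end periods and ICCs of about 0.006 to 0.05, it runs from about 55% to 80%. Reaching 80% requires end periods shorter than a step together with a very small ICC.

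These illustrations work on the plan's own scale of means, with a constant within-ward correlation. They contain no small-sample correction for six clusters, which would lower power further.

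**What to change.** In the Sample size section, recompute the design effect for the step layout in Fig. 1 with period terms and a ward effect. State the number of steps, the period lengths, and the ICC with a range. Then restate the power for 35 versus 50 days, or the difference detectable with 80% power, that 732 participants deliver. Keep the enrolment target. If 1.75 already is the stepped-wedge design effect for that layout, describe it as such, with its ICC, instead of attributing it to ward clustering.

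The cost is a recalculation and a rewritten paragraph, with no extra participants. The downside is that the stated power probably becomes less favourable.
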